## Abstract

**Background:**

Concussion in children and adolescents is a significant public health concern, with 30% to 35% of patients at risk for prolonged emotional, cognitive, sleep, or physical symptoms. These symptoms negatively impact a child’s quality of life while interfering with their participation in important neurodevelopmental activities such as schoolwork, socializing, and sports. Early psychological intervention following a concussion may improve the ability to regulate emotions and adapt to postinjury symptoms, resulting in the greater acceptance of change; reduced stress; and recovery of somatic, emotional, and cognitive symptoms.

**Objective:**

The primary objective of this study is to assess the feasibility of conducting a parallel-group (1:1) randomized controlled trial (RCT) to evaluate a digital therapeutics (DTx) mindfulness-based intervention (MBI) in adolescents aged 12 to <18 years. The attention-matched comparator intervention (a math game also used in previous RCTs) will be delivered on the same DTx platform. Both groups will be provided with the standard of care guidelines. The secondary objective is to examine intervention trends for quality of life; resilience; self-efficacy; cognition such as attention, working memory, and executive functioning; symptom burden; and anxiety and depression scores at 4 weeks after concussion, which will inform a more definitive RCT. A subsample will be used to examine whether those randomized to the experimental intervention group have different brain-based imaging patterns compared with those randomized to the control group.

**Methods:**

This study is a double-blind Health Canada–regulated trial. A total of 70 participants will be enrolled within 7 days of concussion and randomly assigned to receive the 4-week DTx MBI (experimental group) or comparator intervention. Feasibility will be assessed based on the recruitment rate, treatment adherence to both interventions, and retention. All outcome measures will be evaluated before the intervention (within 7 days after injury) and at 1, 2, and 4 weeks after the injury. A subset of 60 participants will undergo magnetic resonance imaging within 72 hours and at 4 weeks after recruitment to identify the neurophysiological mechanisms underlying the potential benefits from MBI training in adolescents following a concussion.

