## Methods

### Trial Design

The proposed study is a Health Canada–regulated parallel-group (1:1) RCT, where patients within 7 days of a concussion will be randomly assigned to one of the two groups: (1) experimental group (n=35), early introduction of the DTx MBI program and (2) control group (n=35), sham DTx attention-matched comparator intervention. The participants will start the intervention the next day after being enrolled in the study. After 4 weeks, those in the experimental group will be offered the MBI program with 4-week additional education modules. Those who are part of the control group will be offered to cross over to start the DTx MBI. Of the 70 participants enrolled, 60 (86%) consenting participants (n=30, 50% from the experimental group and n=30, 50% from the control group) will be enrolled in neuroimaging, which requires participation in a brain scanning session within 72 hours of enrollment and during week 4 of the study. For a schematic diagram of the trial design, procedures, and stages, refer to the study flow diagram in Figure 1.

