##### Intervention Satisfaction

*Intervention satisfaction* will be assessed with the modified version of the Client Satisfaction Questionnaire [52]. This is a validated, reliable, 8-item questionnaire used to measure client satisfaction with a particular program or service. In this case, the questionnaire has been modified to assess participant satisfaction with the digital intervention. The intervention will be deemed satisfactory if >70% of the participants score above the midpoint on the questionnaire [52]. Intervention satisfaction will be assessed at 4 weeks after the enrollment (end of the intervention).

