##### Symptom Burden

*Symptom burden* will be measured in the ED or at 360cc (both retrospective and postinjury acute symptoms) and at 1, 2, 4, and 8 weeks after enrollment using the Health and Behavior Inventory (HBI) [3]. The HBI is a 20-item self-report questionnaire that uses a 4-point Likert scale, with a total range 0-60. It provides scores for cognitive and somatic symptom scales. Emotional symptoms and sleep disturbances will be assessed using the Post-Concussion Symptom Inventory (PCSI) [59-61]. The PCSI [59,60] is a validated, reliable, comprehensive, and self-administered instrument [59-61]. For the purpose of this study, the emotional and sleep domains of the PCSI adolescent scale version (20-item, 7-point Likert scale) will be used. The domains will be assessed in the ED or at 360cc and at 2, 4, and 8 weeks after enrollment.

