#### Covariate Measurements

Information about injuries will be collected from medical records and medical personnel using a standardized case report form. Details regarding the injury and acute signs and symptoms of concussion (ie, loss of consciousness, Glasgow Coma Scale scores, mechanism of injury, neurological status, and other clinical features) will be collected by RAs, with clarification by physicians when necessary. The data will be verified by the site investigator. To calculate the 5P clinical risk score [2], balance will be evaluated by the RA using the balance error scoring system [81], a widely used instrument in the field of sports concussion [82] for objective assessment of postural stability. Pubertal status will be measured using a puberty questionnaire [83]. The questionnaire is a 5-item, self-administered rating scale for pubertal development without pictorial representations or interviews. Demographic data (ie, household annual income and parental education level) will be used as a proxy of socioeconomic status (SES). SES will be collected to assess whether randomization is equally distributed in both groups. If SES is not equally represented in the sample, it will be controlled for in our analysis.

Studies have shown that physical activity can reduce anxiety, improve mood, and help alleviate postconcussive symptoms [84]. We will evaluate physical activity to ensure balance between groups; physical activity levels will be assessed using the Godin-Shepard Leisure-Time Physical Activity Questionnaire [85] on day 1 and then at 2, 4, and 8 weeks after injury.

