#### Follow-Up Procedures

The proposed duration of the app-based MBI is 4 to 8 weeks. After 4 weeks, all participants in the experimental group will be given the opportunity to pursue the MBI for an additional 4 weeks. At that time, participants in the control group will be offered to cross over and start the MBI intervention.

Participants will complete electronic follow-up questionnaires on REDCap at 1, 2, 4, and 8 weeks after enrollment and will have an in-person follow-up at 4 weeks for the cognitive assessment (and the MRI scan for a subset of participants). Cognitive testing will be conducted before brain scanning.

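### The follow-up clock is contradictory: the Abstract and the physical-activity text count weeks from injury, most of the Methods count from enrollment, and the sections on scan timing disagree with one another

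*Protocol article*

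**What the plan says.** **Counted from injury or concussion.** The Abstract's Objective places the secondary outcomes, ending with "anxiety and depression scores at 4 weeks after concussion". The Abstract's Methods place all outcome measures "at 1, 2, and 4 weeks after the injury". In the body, Covariate Measurements times the physical activity questionnaire "on day 1 and then at 2, 4, and 8 weeks after injury".

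**Counted from enrollment.** Follow-Up Procedures, which governs the electronic questionnaires, says: "Participants will complete electronic follow-up questionnaires on REDCap at 1, 2, 4, and 8 weeks after enrollment". Symptom Burden agrees: "at 1, 2, 4, and 8 weeks after enrollment using the Health and Behavior Inventory". The same origin appears in the Table 2 footnote on credibility and expectancy, in Treatment Expectancy, Self-Efficacy, Resiliency, Anxiety and Depression, and Mindfulness, and in the Discussion for the effect sizes on quality of life and symptoms. Intervention Satisfaction ties this clock to treatment: "Intervention satisfaction will be assessed at 4 weeks after the enrollment (end of the intervention".

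**No origin named.** Quality of Life, Fatigue, and the section on attention, working memory and executive function refer only to the 4-week or 8-week follow-up.

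**Imaging.** Trial Design counts the first scan's 72 hours from enrollment; Imaging Measurements and Neuroimaging Procedures count them from injury. The second scan is 4 weeks after recruitment in the Abstract, in week 4 of the study in Trial Design and Imaging Measurements, and 4 weeks after injury in Neuroimaging Procedures.

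**The concern.** The two origins would be interchangeable only if enrollment always fell on the day of injury. Trial Design allows a lag: "patients within 7 days of a concussion will be randomly assigned". It also starts the intervention on the day after enrollment. A 4-week visit counted from injury therefore comes before the end of a 4-week course for anyone enrolled after the day of injury, and the shortfall grows with the lag.

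The secondary objectives include generating estimates for the sample size of a multicenter trial, and the Discussion plans effect sizes for quality of life and symptoms. The Background also names learning the best time points for outcome collection as part of the purpose. A mean or SD taken at an undefined point in treatment and recovery serves these aims poorly. For imaging, the choice of origin also decides which participants can have the first scan inside its window at all.

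**Working it through.** The plan gives no figure to reproduce here. The check is calendar arithmetic plus a comparison of sections.

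**Inputs.** Injury is day 0. Enrollment is on day e, from 0 to 7 (Abstract, Methods; Trial Design). Treatment starts on day e + 1 (Trial Design). The course is 4 weeks, or 28 days (Abstract, Methods).

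**Formulas.**
- Week 4 on the injury clock: day 28. Week 4 on the enrollment clock: day e + 28. Difference: e days.
- Treatment day reached on day 28: 28 − (e + 1) + 1 = 28 − e. Completed days before it: 27 − e.
- End of course: day e + 28 counting inclusively, or e + 29 counting 28 elapsed days.

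| Enrolled on day | Treatment starts | Course ends | Treatment day at injury-clock week 4 | Days short of course end | Enrollment-clock week 4 |
|---|---|---|---|---|---|
| 0 | 1 | 28–29 | 28 | 0–1 | day 28 |
| 1 | 2 | 29–30 | 27 | 1–2 | day 29 |
| 3 | 4 | 31–32 | 25 | 3–4 | day 31 |
| 5 | 6 | 33–34 | 23 | 5–6 | day 33 |
| 7 | 8 | 35–36 | 21 | 7–8 | day 35 |

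For e = 7 the exposure at the injury-clock week-4 visit is 21/28 = 75% counted inclusively, or 20/28 = 71% in completed days. On the enrollment clock the visit falls 0 to 1 day from the end of the course for every e.

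**Week 1.** On the injury clock this is day 7. For e = 6 it falls on the first treatment day. For e = 7 it falls one day before treatment and coincides with enrollment, so it repeats baseline.

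**First scan.** Counted from injury, 72 hours ends on day 3, which participants enrolled on days 4 to 7 cannot meet. With the 48-hour tolerance in the Exclusion Criteria the limit is 72 + 48 = 120 hours, or day 5, and those enrolled on days 6 and 7 still cannot meet it. Counted from enrollment, 72 hours runs to day 7 + 3 = 10 after injury for the latest enrollee.

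**Second scan.** Target dates 4 weeks after injury and 4 weeks after recruitment differ by e days. The stated tolerance is 5 days either way, so for e = 6 or 7 one target lies outside the tolerance around the other.

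**Physical activity against symptoms.** In Table 3 the physical activity questionnaire and both symptom inventories are ticked in the same follow-up columns: Day 14, Week 4 and Week 8. The physical activity schedule also begins at day 1, which the data collection text places on the day after the emergency department or clinic visit, so it starts from an enrollment-based day.

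**The case against.** The strongest defense is that the operational text already settles the questionnaire clock. Follow-Up Procedures says "electronic follow-up questionnaires on REDCap at 1, 2, 4, and 8 weeks after enrollment", most outcome sections agree, and week 4 after enrollment is expressly the end of treatment. For the questionnaires, the injury clock appears only in two Abstract sentences and one clause about a covariate. This largely stands. A reader might infer that the trial will score week 4 before treatment ends; the documents show only that this would follow if the Abstract's rule were applied.

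A reader might also infer that physical activity and symptoms at one visit could be measured up to 7 days apart. Table 3 does not support that, since it puts them in the same columns. The clause in Covariate Measurements is better read as a wording error inside an enrollment-based schedule.

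It is also fair to say that the primary outcomes are feasibility proportions, that no sample-size or power figure changes, and that the lag is fixed before randomization and so falls on both arms alike. Variation in time since injury at week 4 comes with any 7-day enrollment window, so it is no argument against the enrollment clock.

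Two things survive. The Abstract states a timing rule for all outcomes that would give wrongly timed secondary data if followed. And the imaging conflict lies within the Methods, where no section takes precedence over another.

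**Conclusion.** The contradiction is real and should be corrected, with moderate consequences. The two clocks differ by 0 to 7 days. In the extreme case, enrollment on day 7, the injury clock puts week 4 7 to 8 days before the course ends, at 71% to 75% of treatment, and puts week 1 before treatment begins. These limits assume enrollment as late as day 7 and start of treatment the next day, both as stated. The documents give no distribution of the lag, so a typical shift cannot be calculated.

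The effect is confined to the secondary and imaging estimates intended for the next trial. It does not touch the feasibility sample size or power, and it introduces no systematic difference between arms. The imaging timing is the least resolved part.

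**What to change.** 1. In the Abstract (Objective and Methods) and in Covariate Measurements, replace the injury origin with the enrollment origin already used in Follow-Up Procedures and Intervention Satisfaction. Follow-Up Procedures needs no change.
2. Reconcile the Abstract, Trial Design, Imaging Measurements and Neuroimaging Procedures to one stated origin for each scan, and tie the tolerances in the Exclusion Criteria to that origin. If injury is kept for the first scan, say how participants enrolled too late to meet it are handled.
3. Add days from injury to scan, or from injury to enrollment, as a covariate in the imaging regressions described under the nested neuroimaging study. It can be derived from the injury date, which the 7-day eligibility criterion already requires. No corresponding change applies to the questionnaire outcomes, for which the article states no between-arm model.

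The cost is a few wording changes and one degree of freedom in each imaging model, with no new data collection.

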**Results:**

The recruitment began in October 2022, and the data collection is expected to be completed by September 2024. Data collection and management is still in progress; therefore, data analysis is yet to be conducted.

**Conclusions:**

This trial will confirm the feasibility and resolve uncertainties to inform a future definitive multicenter efficacy RCT. If proven effective, a smartphone-based MBI has the potential to be an accessible and low-risk preventive treatment for youth at risk of experiencing prolonged postconcussion symptoms and complications.

**Trial Registration:**

ClinicalTrials.gov NCT05105802; https://classic.clinicaltrials.gov/ct2/show/NCT05105802

**International Registered Report Identifier (IRRID):**

DERR1-10.2196/57226

## Introduction

### Background and Rationale

Approximately 30% to 35% of the children and adolescents who experience a concussion are considered to have persisting symptoms after concussion (PSAC) [1,2], defined as the persistence of somatic (eg, headache, dizziness, and fatigue); cognitive (eg, memory, concentration, and confusion); and other physical, psychological, and behavioral changes lasting beyond 1 month [3]. PSAC may impair daily activities including schoolwork, socializing, and sports and thereby reduce the quality of life (QoL) [4]. Studies have demonstrated that both noninjury and injury factors predict PSAC following a concussion [2,5,6], with the contribution of injury factors to PSAC decreasing over time. However, premorbid conditions such as preinjury somatic symptoms [7], migraine [2], preinjury cognitive ability [8], preexisting attention and mood concerns [9], anxiety [10], and coping strategies [11] remain important predictors of symptom persistence over time [8,12]. Preventive, early rehabilitation programs such as interventions focusing on building psychological resiliency, emotional regulation, and self-efficacy might be key to managing concussions, reducing PSAC risk, and promoting neural recovery.

Mindfulness-based interventions (MBIs) are *present-centered* interventions that encourage acceptance of thoughts and emotions as they occur in the moment without judgment. MBIs have been demonstrated to improve attentional focus, cognitive flexibility, depression and anxiety symptoms, self-concept, resiliency, and academic achievements as well as reduce affective reactivity and fear in clinical youth samples [13]. In addition, in-person MBIs seem effective at treating preinjury predictors of PSAC, such as mood disorders [14-17], somatization-related illness [14,18,19], headache disorders [20], and chronic pain [21]. However, in-person interventions may not be suitable for adolescents with acute concussion owing to high cost and low accessibility [22,23] and require commitment from parents and children for in-person weekly meetings for periods varying from 8 to 16 weeks. Brief (as short as 3 days to 4 weeks) web-based MBIs with guided meditation have been shown to have positive effects on anxiety, negative mood, perceived stress, and attention in different clinical populations [24-27]. MBIs may foster adaptive coping, increase resiliency, and reduce the risk of PSAC following pediatric concussion. Smartphone, or mobile, apps may present a versatile and personalized platform for the delivery of a dedicated MBI for populations experiencing a concussion [28].

Health care digital therapeutics (DTx; smartphone app) have gained popularity in the past decade as a means of screening patients, monitoring symptoms, and delivering psychoeducation and interventions [28,29]. The efficacy of mobile apps in delivering psychological interventions has been demonstrated in mental health samples, particularly in the treatment of depression and anxiety. Randomized controlled trials (RCTs) have shown that app-based interventions can effectively improve depressive and anxiety symptoms compared with waiting list, alternative care, or control conditions [29-34]. Similarly, a recent meta-analysis of RCTs on app-based MBIs has demonstrated significant small-to-medium effects in improving perceived stress, symptoms of depression and anxiety, QoL, psychological well-being, and positive affects, compared with control conditions, waitlist, and alternative interventions [35]. However, the application of an app-based MBI in pediatric concussion has not yet been studied.

We partnered with Mobio Interactive Inc (Toronto, Ontario, Canada), the creator of a clinically validated platform called *AmDTx*, to create an app-based dedicated DTx MBI for pediatric concussion. We assessed the acceptability and usability of the DTx with a small open-label single-arm study (N=10) [36]. The participants reported high satisfaction and found the app easy to use and the treatment to be credible. They also developed a strong alliance with their MBI guides (ie, those who are leading the meditation and psychoeducation sessions) [37]. The primary aim of this study is to assess the feasibility of the 4-week planned RCT methods to determine whether we can advance to an efficacy trial and, thereby, elevate our understanding of the optimal time points for collecting outcome measures. At 4 weeks, those randomized to the DTx MBI will have the opportunity to continue for another 4 weeks, that is, completing a total of 8 weeks of MBI. The goal of this additional 4-week intervention is to explore feasibility outcomes in an 8-week intervention. Finally, those who are part of the DTx control group (attention-matched comparator intervention) will have the opportunity to cross over to the DTx MBI group.

### Primary Research Objective

The primary research objectives are to assess the feasibility of conducting a larger RCT by evaluating recruitment efficiency, adherence to treatment, credibility, and retention.

### Secondary Research Objectives

The **s**econdary research objectives were as follows:

Establish the participants’ expectancy toward both interventions.Examine the participants’ satisfaction with the interventions.Generate estimates to inform sample size calculations for a future multicenter RCT.Assess whether there is preliminary evidence of an efficacy signal for QoL, fatigue, symptoms, resiliency, self-efficacy, cognition, anxiety, depression, and mindfulness.Examine the experimental group’s baseline characteristics, adherence, and attrition rates in those who chose to continue for an additional 4 weeks compared with those who chose to complete the study at 4 weeks compared with those who were lost to follow-up.Examine the control group’s baseline characteristics, adherence, and attrition rates in those who chose to cross over to the experimental interventions at 4 weeks versus those who chose to complete the study at 4 week versus those who were lost to follow-up.Examine whether the experimental intervention is associated with differential brain-based imaging patterns of functional connectivity, cerebral blood flow, and spectroscopy.Examine safety by examining whether the experimental intervention has increased adverse events (ie, total number) relative to the control intervention.

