## Discussion

First, we will use this study to examine the feasibility of our RCT methods, including delivering a DTx-containing MBI to participants who are acutely or subacutely concussed, and whether we can move to the efficacy trial. Second, to better inform our larger RCT, this study will allow us to estimate the effect sizes of QoL and the symptoms at 4 and 8 weeks after enrollment compared with those randomized to the control group (sham intervention). Third, we will use this study to assess whether MBI induces measurable brain-based effects, that is, examine whether the intervention modulates neuroimaging indicators such as functional connectivity. This trial will offer insight into a cost-effective way to manage pediatric concussion in the acute and subacute phases of injury. This study will help support the development of a future full-efficacy trial to assess the effectiveness of the intervention in increasing QoL and decreasing the concussion symptom burden.

The development of an intervention to increase adaptive interpersonal qualities in acute settings is important for reducing the risk of PSAC. Formal in-person MBIs such as mindfulness-based stress reduction have been shown to increase perceived self-efficacy and teach positive acceptance of change [13]. However, these interventions may not be suitable for a youth population with acute concussion as they are costly and not easily accessible. A brief web-based MBI with guided meditation had positive effects on anxiety, negative mood, perceived stress, and attention in different clinical populations [24-27]. Furthermore, a 3-week RCT using the DTx MBI within *AmDTx* increased stress resilience and attentional control in university students self-described as experiencing mild anxiety [27]. The customization of a novel MBI, designed in collaboration with MBI therapists, patients, and Mobio Interactive, will bring a required concussion treatment into the homes of all patients, with the goal of increasing adaptive skills and cognitive performance, promoting neural recovery, and reducing the risk of PSAC. If found to be effective, DTx MBI holds promise as an accessible and low-risk preventative treatment for youth at risk for prolonged postconcussion symptoms and sequelae.

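### Two secondary objectives compare attrition across groups that are themselves defined by attrition, and weeks 5-8 of the MBI are seen only in participants who opt in

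*Protocol article*

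**What the plan says.** All references are to the protocol article. Under Secondary Research Objectives, the experimental-arm objective is to "Examine the experimental group’s baseline characteristics, adherence, and attrition rates in those who chose to continue for an additional 4 weeks". Continuers are one of three groups; the same sentence names the other two: "compared with those who chose to complete the study at 4 weeks compared with those who were lost to follow-up". The control-arm objective has the same three-part structure, setting "those who chose to cross over to the experimental interventions at 4 weeks versus those who chose to complete the study at 4 week", and both against those lost to follow-up.

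Background and Rationale gives the reason for the extension: "The goal of this additional 4-week intervention is to explore feasibility outcomes in an 8-week intervention". Entry to it is optional. Follow-Up Procedures says that after 4 weeks "all participants in the experimental group will be given the opportunity to pursue the MBI for an additional 4 weeks", and that controls may cross over to the MBI. Under the description of the experimental intervention, participants who end at week 4 go straight to the closing module, and only those who continue receive modules 5 to 8.

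Two statements limit the reach of the point. Follow-Up Procedures also says "Participants will complete electronic follow-up questionnaires on REDCap at 1, 2, 4, and 8 weeks after enrollment", with no restriction to continuers. The Discussion plans to "estimate the effect sizes of QoL and the symptoms at 4 and 8 weeks after enrollment compared with those randomized to the control group", which is a comparison by randomised group.

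**The concern.** Attrition is listed as a variable to compare, yet the groups being compared are attrition categories. A table built to this wording would show differences in attrition that are fixed before any data are collected.

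Adherence has a related problem. The three groups spend different lengths of time on the intervention: up to 8 weeks, 4 weeks, or until loss. In the control arm, a crossover's use before week 4 is of the math game and use afterwards is of the MBI. The objectives name no common window, so a difference in adherence could reflect time on study, or which intervention was in use, as much as behaviour.

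The extension is also meant to inform the feasibility of an 8-week intervention. Use of modules 5 to 8 can be observed only in participants who stayed to week 4 and then asked for more. A later trial that assigned 8 weeks from the start would have no such filter. If the continuers' rate were quoted alone, the 8-week programme would probably look more feasible than it is.

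**Working it through.** **The plan's own use of attrition.** The Feasibility Objective under Statistical Power needs 55 participants for adherence and allows about 20% loss. 55 / (1 − 0.20) = 68.75, rounded up to 69, which agrees with the stated 70 given the approximate rate. The stated powers multiply to 1.000 × 0.999 × 0.958 × 0.958 × 0.987 = 0.905, matching the stated 90.5%. None of this depends on the two objectives discussed here.

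**Attrition by group, to week 4.** Inputs are 35 per arm (Trial Design) and 20% loss (Statistical Power). The lost group is read as those lost by week 4; the article does not date the loss.
- Lost by week 4: 35 × 0.20 = 7. Retained: 35 − 7 = 28.
- Attrition in the lost group: 7/7 = 100%.
- Attrition in those who complete at 4 weeks: 0%. In those who continue or cross over: 0%, since both had to be present at week 4 to choose.
- The informative figure is 7/35 = 20% of those randomised.

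The 100% / 0% / 0% pattern holds for any loss rate above zero. Only loss after week 4 among continuers or crossovers is free to vary, and the other two groups provide no comparator for it.

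**Weeks 5-8 of the MBI, two denominators.** Let c be the share of retained participants who continue and q the share of continuers who adhere. The article gives neither, so both are assumptions.
- Rate among continuers = q.
- Rate per randomised = 0.80 × c × q.

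With c = 50% and q = 80%: continuers 28 × 0.50 = 14; adherent 14 × 0.80 = 11.2; per randomised 11.2/35 = 32%, against 80% among continuers.

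| c | continuers | q = 70% | q = 80% | q = 90% |
|---|---|---|---|---|
| 25% | 7 | 14% | 16% | 18% |
| 50% | 14 | 28% | 32% | 36% |
| 75% | 21 | 42% | 48% | 54% |

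Cells are rates per randomised participant. The gap between denominators is wide throughout. The continuers' rate is also imprecise: the 95% half-width near 50%, 1.96 × √(0.25/n), is about 37 points for n = 7, 26 for n = 14 and 21 for n = 21.

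**Who is followed to week 8.** The objectives describe some participants as completing the study at 4 weeks, while Follow-Up Procedures schedules week-8 questionnaires for participants generally. Taken together, these do not show whether someone who stops at week 4 is assessed at week 8.

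**The case against.** The strongest reply is that these are secondary, descriptive objectives in a condensed article. The wording might loosely mean the share of each arm in each category, which is not circular, and denominators are often left to an analysis plan that is not shown. Comparing baseline characteristics across the three groups is legitimate, as is comparing adherence before the choice. That much stands, and it lowers the severity. It does not rescue the attrition comparison: the text names attrition as a variable examined within the groups and does not say that disposition shares are meant.

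A reader might infer four stronger claims that the documents do not support:
- **That every 8-week figure describes only continuers.** The week-8 questionnaires are not limited to them, and the Discussion compares by randomised group.
- **That adherence in the lost group is low by definition.** Adherence comes from in-app use and retention from completing assessments, so a participant can stop one and keep the other. Adherence there may be truncated, but it is not fixed.
- **That 8-week rates will be judged against the green limits.** Table 2 sets no 8-week criterion, and the article says "The primary aim of this study is to assess the feasibility of the 4-week planned RCT methods".
- **That the continuers' rate is an upper bound for an assigned programme.** In the example, if all 14 who stopped and all 7 who were lost would have adhered, the rate would be (11.2 + 21)/35 = 92%, above 80%. Nor does declining an optional extension show that a participant would fail an assigned 8-week course, so 32% is not a forecast.

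**Conclusion.** The point holds in a limited form. As worded, the attrition comparison to week 4 is determined by how the groups are defined, in both arms, and cannot answer its own question. Adherence across the groups is not interpretable without a common window. Adherence to and attrition from weeks 5-8 of the MBI are conditional on opting in and are probably optimistic for an assigned 8-week programme. The illustrative contrast of 80% against 32% rests on the plan's 20% loss and on assumed continuation and adherence shares; its size is uncertain, but the two denominators differ clearly across the whole range shown. Severity is low, because the objectives are secondary and exploratory and the 4-week primary criteria, sample size and power are unchanged.

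**What to change.** Reword the two objectives and fix the tabulation:
1. Keep the three-way comparison for baseline characteristics and for adherence over a common window before the week-4 choice, for example weeks 1-4, or up to loss with time on study shown.
2. Report attrition as disposition, with all randomised per arm as denominator: lost by week 4, stopped at week 4, continued or crossed over, lost by week 8.
3. Report 8-week MBI adherence and retention both among continuers and per all randomised to MBI. Label the first as conditional on opting in and the second as per randomised participant, and call neither a bound.
4. Reconcile the objectives' description of participants completing the study at 4 weeks with the week-8 questionnaires in Follow-Up Procedures, stating who is followed to week 8.

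The cost is wording and tabulation only, with no change to sample size. The 8-week per-randomised figures will look less favourable than those among continuers.
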